## **Background and project description**

### **Myalgic Encephalomyelitis/Chronic Fatigue Syndrome**

Myalgic Encephalomyelitis/Chronic Fatigue Syndrome (ME/CFS) is a disease of unknown etiology characterized by post-exertional malaise (PEM), sleep disturbances with inadequate restitution, fatigue, pain and sensory hypersensitivity, autonomic dysfunction, cognitive impairment, and several other symptoms. The diagnosis relies on exclusion of other disorders associated with fatigue. There is no validated specific and sensitive biomarker, and no standard approved effective treatment.

Using the Canadian consensus criteria (1), an estimated 0.1-0.8% of the population suffer from ME/CFS (2, 3), which must be distinguished from the much more common general fatigue.

ME/CFS has profound impact on quality of life for patients and their caretakers (4, 5). The socio-economic costs are very high, and there is an urgent need for elucidation of the disease mechanisms, for improved diagnostic approaches, and for rational treatment (6).

ME/CFS often starts in previously healthy individuals after an infection, the most common being infectious mononucleosis (Epstein-Barr virus). It is 3-4 times more frequent in women and influenced by genetic predisposition (7).

The severity varies between patients who are able to participate to some extent in social life (mild), those who are mainly housebound (moderate) or bedridden (severe), and the very severely ill who are completely dependent on assistance for all daily living tasks like feeding or turning around in bed.

### **Previous clinical trials**

Our interest in ME/CFS started in 2007 in our cancer ward, when we observed patients with long-standing ME/CFS who got cancer, and who independently reported that the cancer treatment had beneficial effects on their ME/CFS. The treatments included the cytotoxic drug cyclophosphamide and/or the monoclonal B-cell depleting anti-CD20 antibody rituximab. Our observations led to the working hypothesis that ME/CFS in a subgroup could be a variant of an autoimmune disease, often with a post-infectious onset and with a role for B-cells/plasma cells and antibodies.

Based on this hypothesis, we have during the last 12 years tested relevant immunomodulatory drugs in clinical trials for ME/CFS patients. Our clinical trials evaluating the anti-CD20 B-cell depleting antibody rituximab in ME/CFS patients include:

- a pilot case series (8), a small randomized phase II study with a negative primary and positive secondary endpoints (9),
- an open-label phase II study with rituximab maintenance with long-lasting clinical responses in half of patients (10),
- a randomized, multicentre, double-blind and placebo-controlled phase III trial which was negative for the outcome measures (11).

Factors that may have influenced the outcome of the phase III trial include heterogeneity among patients, placebo mechanisms, natural symptom variation, and non-optimal outcome measures.

We also performed an open-label phase II trial using cyclophosphamide intravenous infusions, with clinical responses in half of patients and long-lasting clinical benefit up to four years (12). Cyclophosphamide has broad effects on several subsets of lymphocytes, and the mechanism for benefit in ME/CFS could involve the anti-proliferative effects inhibiting the B-cell activation to plasmablasts. Although there were no severe side effects in our study, cyclophosphamide can induce infertility, and a broader use in ME/CFS patients may be problematic due to toxicity concerns.

Further, we have also seen symptom improvement in ME/CFS patients using bortezomib which mainly targets plasma cells. However, this proteasome inhibitor is also associated with toxicity concerns.

Our pooled experience supports that some ME/CFS patients do respond to rituximab and B-cell depletion, and/or cyclophosphamide. As rituximab targets CD20 positive B-cells, patients whose autoantibody production occurs in CD20 positive (early) plasmablasts would be likely responders. In most patients, however, autoantibodies may be produced in CD20 negative, long-lived plasma cells, which are not targeted by rituximab. This is a known mechanism for lack of response to rituximab in several established autoimmune diseases.

### Pathomechanisms

We have recently published an invited viewpoint article in the Journal of Clinical Investigation, focusing on pathomechanisms and possible interventions in ME/CFS (13). In brief, we suggest that ME/CFS is a variant of an autoimmune disease, with a role for B-cells/plasma cells and a pattern of autoantibodies emerging after infection. The alleged pathomechanism and possible targets for intervention are shown in Figure 1 below, copied from our JCI article (13).

Several findings support an autoimmune disease mechanism in ME/CFS. These include a marked female preponderance, a high frequency of autoimmunity among first-degree family members (40-55% in our trials) and enriched HLA risk alleles (14). Furthermore, elderly ME/CFS patients have an increased risk of B-cell lymphoma, especially the low-grade marginal zone lymphomas often associated with autoimmunity or chronic infections (15). Serum B-cell activating factor

(BAFF) increase (16), skewed B-cell receptor gene usage (17), and gene expression studies suggesting antigen driven B-cell clonality (18) or altered B-cell differentiation (19), may point to B-cell involvement. In addition, beneficial clinical effects have been reported after immunoadsorption to remove plasma IgG (20).

In established autoimmune diseases, pathogenic IgGs often associate with complement activation, inflammation, and tissue injury. These features are not characteristic of ME/CFS. We suggest that a variant of an autoimmune mechanism affects the autonomic control of blood vessel tone and flow autoregulation. Key symptoms may result from autoantibody-mediated functional disturbance in blood flow autoregulation causing tissue hypoxia on exertion, with secondary autonomic and metabolic responses to maintain energy homeostasis (21). This is associated with lactate accumulation from limited exertion, in some patients even at rest.

There is growing evidence for endothelial dysfunction in ME/CFS affecting large arteries assessed by flow-mediated dilation (FMD), and small arteries assessed by post-occlusive reactive hyperemia (PORH) (22-24). Also, reduced central venous pressure and impaired venous return (“preload failure”) with inadequate cardiac output on exertion, and inadequate oxygen extraction in peripheral tissues due to arteriovenous shunting have been demonstrated (25, 26), possibly due to neurovascular disturbances. These findings could not be explained by deconditioning due to long-lasting disease and inactivity.

Such circulatory disturbances would cause secondary and compensatory adaptations, such as altered autonomic function with increased sympathetic tone. Dysregulated autonomic function has been repeatedly demonstrated in ME/CFS during the last decades (27, 28). A state of inadequate autoregulation of blood flow with hypoxia on exertion would cause secondary metabolic adaptations in efforts to restore energy balance, with increased use of fatty acids and amino acids for fueling and oxidative phosphorylation, also repeatedly shown (21, 29, 30).

[figure not shown]

ME/CFS partly overlaps clinically with postural orthostatic tachycardia syndrome (POTS), orthostatic intolerance, fibromyalgia, and complex regional pain syndrome (CRPS). We believe

that these illnesses may be associated with a pattern of autoantibodies occurring after triggers such as systemic infections (31), but not resolving properly over time. In ME/CFS, a persistent functional autoantibody pattern could disturb blood vessel autoregulation and lead to secondary metabolic and autonomic adaptations.

To this end, functional G-protein coupled receptor (GPCR) autoantibodies may be involved (32). Agonistic autoantibodies to  $\beta$ 2 adrenergic receptors (AR) and muscarinic 3 receptors have been demonstrated in orthostatic hypotension (33). In POTS, an autoimmune basis has been suggested by the presence of several functional autoantibodies towards GPCRs affecting blood pressure and heart rate regulation, such as antibodies to  $\alpha$ 1AR,  $\beta$ 1AR and  $\beta$ 2AR (34), and angiotensin II type 1 receptor. Autoantibodies to GPCRs including adrenergic and muscarinic receptors have been investigated in ME/CFS (35). Although GPCR autoantibodies are also present in healthy individuals, it is possible that they contribute in regulatory networks associated with different physiological states and with disease (36).

Thus, we suspect that the autoantibodies in ME/CFS are not complement-activating, nor associated with the histologic inflammation and tissue damage that are seen in many classic autoimmune diseases. Instead, there may be a functional impairment of blood vessel function and autonomic regulation, caused by a pattern of naturally occurring autoantibodies persisting beyond the expected course after the initial infection. Possibly, these naturally occurring autoantibodies are anti-idiotypic (Ab2) and directed against the Fab-fragment of primary antibodies (Ab1) from the infection, and therefore representing “mirror images” of the initial antigen (such as e.g. the spike protein in SARS-CoV2). The anti-idiotypic (Ab2) antibodies may therefore activate or inhibit the cellular structures, and offer an explanation for the presumed natural occurrence with agonist or antagonist activity (37).

### Plasma cell targeting

If our interpretations regarding B-cells/plasma cells and autoantibodies in ME/CFS hold true, the production of autoantibodies in a majority of the patients takes place in the mature, long-lived plasma cells. Long-lived plasma cells are refractory to B-cell depletion or to ordinary immunosuppressive drugs (38, 39), and as such, B-cell depletion using rituximab would only be effective as intervention in a minority of patients. Thus, plasma cell targeting and immunoglobulin manipulation emerge as therapeutic opportunities to be explored in approved clinical studies. Possible trials could include drugs that reduce serum IgG by targeting Fc receptor neonatal (FcRn), anti-BAFF antibody targeting B-cell activating factor or anti-CD38 antibodies to target long-lived plasma cells (Figure 1).

Daratumumab is a humanized IgG1k monoclonal antibody directed against the CD38 glycoprotein involved in cell adhesion and signal transduction. The CD38 protein is highly expressed on plasmablasts, short- and long-lived plasma cells, but also with weaker protein expression on subsets of macrophages, B-cells including regulatory B-cells, and T-lymphocytes. CD38 is an ectoenzyme with several functions, which catalyzes the conversion of nicotinic adenosine dinucleotide (NAD+) to cyclic adenosine diphosphate ribose (cADPR), and cADPR to ADPR leading to accumulation of adenosine (40).

The drug is approved for use with chemotherapy or as monotherapy for patients with multiple myeloma (41, 42). Formulations for intravenous and subcutaneous administration exist.

We have since 2016 discussed the possibility to explore use of the anti-CD38 antibody daratumumab to target autoantibody-producing long-lived plasma cells in ME/CFS. However, although in vitro data have been available, there has been a scarcity of published data evaluating daratumumab in clinical autoimmune diseases. In the last two years, several small case series have been published demonstrating high efficacy and good tolerability in several treatment-refractory autoimmune diseases, and a role for anti-CD38 antibody therapy in systemic autoimmune diseases has been summarized (43).

In autoimmune hemolytic anemia (44), anti-phospholipid syndrome (45), treatment-refractory autoimmune cytopenias, cold agglutinin disease, and other autoimmune diseases (ITP, systemic lupus, anti-CASPR2 encephalitis, rheumatoid arthritis) daratumumab has shown high efficacy in case series (46). In systemic lupus erythematosus refractory to B-cell depletion, cyclophosphamide and several immunosuppressive drugs, daratumumab was effective and clinical responses sustained by anti-BAFF (belimumab) maintenance treatment (47).

In all these case series, the tolerability to daratumumab has been very good, with no severe infusion-related reactions. The patients should however, be monitored carefully for any side effects, including infusion-related symptoms and episodes of neutropenia.

A trial is also ongoing in Norway (DART study) using daratumumab for the treatment of patients with immunological thrombocytopenia (ITP) ([Project #2052824 - DART-study - Cristin](#)).

Memory B-cells do not express significant CD38, and re-emergence of antibodies over time would be expected. According to our pathomechanistic hypothesis (13), with autoantibodies emerging after infection which persist and target blood vessel regulation, we believe that ME/CFS disease is a reversible disease. We acknowledge that patients may also experience spontaneous remissions. Elucidation of the mechanisms for symptom maintenance is crucial, but it is conceivable that a “resetting” of the plasma cell compartment could induce a sustained remission in some patients.

### Long COVID

Recently, there has been increasing focus on the post-COVID symptoms described as “long COVID”, which in many aspects resemble the symptoms of ME/CFS. This applies particularly to patients with relatively mild initial viral disease and no obvious signs of organ damage, but with sustained fatigue, post-exertional malaise and cognitive impairment (48, 49).

Autoantibodies were detected in 50% of COVID-19 patients compared to 15% of controls (50). In addition, a recent study assessed autoantibodies against the complete “exoproteome” (secreted and extracellular proteins) after COVID-19 infection, showing a myriad of autoantibodies with functional impairment of many important immune related and receptor molecules (51).

Manifested long Covid may in time prove to be an entity where immune manipulation can yield benefits.

## **A pilot study of 10 patients with moderate to severe ME/CFS, using four subcutaneous injections of the anti-CD38 antibody daratumumab, with follow-up for 12 months (KTS-9-2022)**

### **Purpose**

The main purpose is to evaluate feasibility and safety of daratumumab subcutaneous injections in patients with moderate to severe ME/CFS. We will also collect efficacy data.

### **Design**

An exploratory pilot study of six patients with moderate to severe ME/CFS. After inclusion, there will be an initial 12-weeks observational run-in period, followed by administration of 4 subcutaneous injections of the anti-CD38 antibody daratumumab with 2-week intervals. Patients will be subject to clinical follow-up for 40 weeks from start of intervention. Four additional patients will receive the same intervention, and if they show improvement of ME/CFS symptoms by clinical evaluation six weeks after the fourth injection (at study week 24), they will receive three additional maintenance daratumumab injections at weeks 26, 34 and 42.

### **End of study**

The study ends when the last included patient has completed their final visit after 52 weeks. For patients with clinical improvement at week 24, who receive additional three daratumumab injections at weeks 26, 34 and 42, the follow-up period will be extended to week 72.

### **Inclusion**

Following approval from the Regional Ethics Committee and the Norwegian Medicine's Agency, we aim to start recruitment in the summer of 2022. The first two included patients will complete 12 weeks run-in and 6 weeks intervention (18 weeks in total). Subject to a safety review, the remaining four patients will then start intervention. End of follow-up of the last patient is planned at the end of 2024.

Participants will be recruited from available lists of ME/CFS patients who have contacted the study center and requested to be evaluated for possible future clinical studies, and may include participants from previous studies. The candidates will be contacted by telephone or in writing, depending on the mode of contact they have themselves specified.

### **Inclusion criteria**

1. ME/CFS according to Canadian consensus criteria (2003) (1); moderate (mainly housebound) to severe (mainly bedridden) disease.
2. Age 18 to 65 years.
3. Signed informed consent.
4. Duration of ME/CFS disease at least two years.
5. The ME/CFS disease should have a defined onset, e.g. after an initial infection or other immunological trigger.

6. For females of childbearing potential: Negative serum pregnancy test.

### Exclusion criteria

1. Chronic fatigue conditions not fulfilling Canadian consensus criteria.
2. Age under 18 or over 65 years.
3. Mild or mild-to moderate ME/CFS.
4. Very severe ME/CFS, where patient is unable to travel to the hospital for intervention and assessments.
5. Participation in a clinical trial with intervention aimed at ME/CFS during the last two years.
6. Endogenous depression.
7. Known multi-allergy with clinically assessed risk for hypersensitivity to daratumumab.
8. Known contraindication to daratumumab.
9. Significant comorbidity with reduced organ function (kidney, liver, heart, pulmonary).
10. Previous long-term systemic treatment with immunosuppressants the last two years, excluding short steroid courses in e.g. obstructive lung disease.
11. Chronic infections, including chronic hepatitis B or C, HIV, or other relevant infection.
12. Previous or concomitant malignant disease, except basal carcinoma of the skin, or carcinoma in situ in the uterine cervix.
13. Pregnancy or lactation.
14. Inability to comply with protocol including follow-up.

### Evaluations

Evaluation of safety and toxicity at 2-week intervals, for 16 weeks after start of intervention (from week 12 to week 28), then at 4-week intervals for the remaining follow-up (from weeks 29 to 52). For patients with clinical improvement at week 24, who receive additional three daratumumab injections, the evaluation of safety and toxicity will be extended to week 72. This will include registration according to CTCAE ver. 5.0 of adverse events (AE), serious adverse events (SAE), and SUSAR (suspected unexpected serious adverse reactions).

**Questionnaires** at 2-week intervals during the 12-week run-in period, and during the first 16 weeks after start of intervention, then at 4-week intervals for the remaining follow-up period (to week 52 for patients without maintenance, and to week 72 for patients with three additional maintenance injections).

The questionnaires include:

The Short Form (36) Health Survey (SF36).

DePaul questionnaire Short Form (DSQ-SF).

Function level in percent, according to a form with examples.

In addition, patients will complete the Hospital Anxiety and Depression Scale (HADS) questionnaire at baseline, at 24 weeks, and at 52 weeks.

### Fitbit armband data:

Registration of the following variables:

Steps per 24 hours.  
Resting heart rate.  
Heart rate variability.

Mean (and SD) values will be recorded for these variables at 2-week intervals during the 12-weeks run-in period and for 16 weeks from start of intervention (i.e. weeks 0-28), then at 4-week intervals for the remaining follow-up period (from week 29 to week 52).

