### Endpoints and statistical analyses

The primary outcome measures are safety and tolerability as measured by treatment-emergent adverse events.

The secondary objectives for efficacy are changes in outcome variables, from the baseline/run-in period (12 weeks) before intervention, and through 40 weeks follow-up from start of intervention for SF36 domains including SF36 Physical Function (SF36-PF) and SF36 Bodily pain (SF36-BP), DSQ-SF, Self-reported Function level, and Steps per 24 hours.

The pilot study is explorative, with no blinding or placebo group. We will not describe patients dichotomously as responders or non-responders. Rather, the outcome measures will be descriptive, and assessed by changes in the courses of variables from baseline through 52 weeks from inclusion, including a 12-week run-in before intervention, and 40 weeks after start of intervention. For patients receiving additional maintenance injections at weeks 26, 34 and 42, the analyses will be extended through follow-up to week 72. The outcome variables for efficacy will be assessed by General Linear Model (GLM) Repeated measures for time effects, with the baseline values given as mean values for the 12 week run-in period before start of intervention.

We will also perform analyses for changes in outcome measures at fixed time points compared to baseline, at end of run-in period (i.e. at 12 weeks) and again at 16, 18, 20, 22, 24, 28, 32, 40, 48 and 52 weeks, for patients receiving additional maintenance injections extended at four-week intervals to week 72. Differences in outcome measures from baseline, and from end of run-in at 12 weeks, to the fixed time points after intervention will be assessed by paired t-test or by Wilcoxon paired non-parametric tests.

Extended follow-up may be performed also after end of study, either by clinic attendance or by telephone, to monitor any toxicity or ongoing clinical responses.

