### “Run-in” period before intervention

To capture aspects of natural symptom variation over time, patients will receive no intervention during the first 12 weeks of the study, but they will complete questionnaires at 2-week intervals and use the Fitbit armbands for continuous registration of steps per 24 h, resting heart rate and heart rate variability.

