#### **Daratumumab dosing, injection, and injection-related reactions (IRR)**

Daratumumab subcutaneous injections will be given at a fixed dose of 1800 mg. A 15 ml syringe, which also contains recombinant hyaluronidase, is injected over 3-5 minutes into the abdomen approximately 7-8 cm to the right or left of the umbilicus (rotating injection sites for successive injections), on intact, healthy skin.

The patient will stay in the outpatient ward for at least 6 hours after the first Daratumumab injection, for observation of any injection-related reactions (IRR). Intravenous access will be established before the injection for administration of premedication and will be maintained throughout the observation period. Any allergic reactions or IRR will be treated according to standard hospital procedure.

If no IRR after the first injection, the observation period following the subsequent three injections will be 2 hours.

IRR after subcutaneous injections occurred in 9% of patients with multiple myeloma after the first injection, usually of grade 1-2. The risk of IRR will probably be lower in these patients without malignant plasma cells due to the low number of CD38 positive plasma cells. In the small patient series using daratumumab in autoimmune diseases, IRR was not reported to be a clinical problem.

If a patient suffers a severe allergic reaction or injection-related reaction (grade 4), the patient will not receive further daratumumab intervention.

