### Fitbit charge 4 data

Patients will receive a Fitbit Charge 4 armband at study start, with detailed instructions. The patients will be instructed to use Fitbit continuously except when recharging once weekly. Fitbit activity data from each participant will be downloaded at the study centre weekly, using the Fitbit web API (<https://dev.fitbit.com/build/reference/web-api/developer-guide/application-design/>)

After our randomized, placebo-controlled and double-blind trial with rituximab proved negative (11), we have worked to improve the design of future intervention trials in ME/CFS. We recently performed an observational study of 27 ME/CFS patients over 6 months, without intervention, using QoL and disease-specific questionnaires as well as continuous monitoring of steps and resting heart rate.

We will use the set-up from the Fitbit activity study (as yet unpublished). The study was approved by the Regional Committees for Medical and Health Research Ethics in Norway (REK No. 28780). A Data Protection Impact Assessment was performed in consultation with the IT Security Manager and Data Protection Officer for the Bergen Hospital Trust and user representatives.

Fitbit's terms of use comply with the General Data Protection Regulation (GDPR) directive. In order to protect the participants' privacy, we will use pseudonymisation toward third parties. Each participant Fitbit account will be set up using a study-specific e-mail address, initials instead of name and a fictitious date of birth.

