### Possible risks

The participants may experience side effects from the intervention. We cannot be certain that the anti-CD38 antibody treatment will be associated with a beneficial disease course, and patients could in theory also experience worsening of their ME/CFS symptoms.

A lack of clinical response may represent a psychological burden to the patients.

For patients with moderate (mainly house-bound) or severe (mainly bedridden) ME/CFS, participating in a clinical trial may cause temporary worsening due to the stress involved in performing study-specific procedures, such as travelling to the hospital, taking blood samples, receiving subcutaneous interventions and completing questionnaires.

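### Early step-count means each contain a hospital-visit day while the run-in baseline has almost none, so the week 16, 18 and 20 comparisons can partly reflect attendance

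*Protocol*

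**What the plan says.** Protocol, Fitbit armband data, defines the step summary: "Mean (and SD) values will be recorded for these variables at 2-week intervals during the 12-weeks run-in period". The same 2-week spacing runs to week 28, "then at 4-week intervals for the remaining follow-up period (from week 29 to week 52"). Assessment during follow-up repeats this and extends it for maintenance patients. Under Fitbit charge 4 data, "The patients will be instructed to use Fitbit continuously except when recharging once weekly", so hospital days are captured. No section treats them separately.

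Endpoints and statistical analyses lists the efficacy variables as SF-36 domains plus "DSQ-SF, Self-reported Function level, and Steps per 24 hours". All but the last are self-reported. The repeated-measures model uses a run-in baseline, "with the baseline values given as mean values for the 12 week run-in period before start of intervention". Paired tests then compare weeks 16, 18, 20, 22, 24, 28, 32, 40, 48 and 52 with baseline and with week 12.

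On hospital attendance:
- The schedules of activities and Assessment during follow-up place clinic or injection visits at weeks 0, 12, 14, 16, 18, 20, 32 and 52. With maintenance, weeks 26, 34 and 42 are added and the full assessment at week 32 moves to week 34.
- In the run-in, "patients will receive no intervention during the first 12 weeks of the study", and weeks 2 to 10 carry only questionnaires and Fitbit downloads.
- Daratumumab intervention gives the first two patients a 4-6 week observation period between injections 2 and 3.

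**The concern.** Attendance rises when dosing starts and, on the standard schedule, falls back after week 20. It therefore moves in step with treatment in every patient on that schedule, and averaging over patients does not remove it.

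Participants are mainly housebound or mainly bedridden, so a trip to hospital is unlikely to be an ordinary day for steps. The days after it may be unusual too. Under Possible risks the protocol says that "participating in a clinical trial may cause temporary worsening due to the stress involved in performing study-specific procedures, such as travelling to the hospital". A visit could raise the interval mean through extra walking on the day, or lower it through fewer steps afterwards.

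The study is open-label with no control group, so readers will lean on the one efficacy outcome that is not self-reported. A bump or dip at weeks 16 to 20 could be taken for an early drug response, an early worsening, or a response that fades.

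**Working it through.** The protocol states no figure on this point, so there is none to reproduce. The check has two parts.

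**1. Hospital days per interval.** Scheduled visits were counted with intervals that include their last day and again with intervals that include their first day.

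- Standard schedule: intervals 12-14, 14-16, 16-18 and 18-20 hold exactly one visit each under either convention, 1/14 = 7.1% of days.
- Run-in: the intervals from week 2 to week 10 hold none. The 84-day baseline holds one visit (1/84 = 1.2%), or two if both end days count (2/84 = 2.4%).
- First two patients: with a 4-week gap, one of the four intervals from week 12 to 20 has no injection or week-20 visit; with a 6-week gap, two have none.
- Without maintenance, the means ending at weeks 24, 28, 40 and 48 hold no clinic or injection visit. Week 22 holds one only if the week-20 day is counted in 20-22. Weeks 32 and 52 hold at most one day in 28 (3.6%).
- With maintenance, the week-26 visit or its following days fall in the mean ending at week 28, which is why that point is clean only without maintenance.
- NIRS sessions have flexible windows (weeks 12-14, 20-24 and 48-52) and could add a hospital day, including before week 24 or at week 48.

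**2. Shift in a 2-week mean with no drug effect.** The documents give no step counts, so these inputs are assumptions:
- k = visit-day steps divided by usual-day steps, from 1.25 to 4
- d = number of following days at half the usual steps, from 0 to 3
- b = visit days in the 84-day baseline, from 0 to 2

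With f = (k - 1) - 0.5d, shift = (1 + f/14) / (1 + b·f/84) - 1.

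For b = 1:

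| k | d = 0 | d = 2 | d = 3 |
|---|---|---|---|
| 1.25 | +1.5% | -4.5% | -7.6% |
| 1.5 | +3.0% | -3.0% | -6.0% |
| 2 | +5.9% | 0.0% | -3.0% |
| 3 | +11.6% | +5.9% | +3.0% |
| 4 | +17.2% | +11.6% | +8.8% |

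The extremes worked out:
- k = 1.25, d = 3: f = 0.25 - 1.5 = -1.25, so 0.9107/0.9851 - 1 = -7.6%.
- k = 4, d = 0: f = 3, so 1.2143/1.0357 - 1 = +17.2%.

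The last case gives +21.4% with b = 0 and +13.3% with b = 2.

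**Dropping only the visit day.** Take k = 2, d = 2 and an unaffected baseline. The all-day mean is (2 + 2×0.5 + 11)/14 = 1.00, a shift of 0%. Without the visit day it is (2×0.5 + 11)/13 = 0.923, a shift of -7.7%. Dropping the visit day alone can create a bias that the all-day mean did not have.

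**The case against.** Which wearable days count is often left to a statistical analysis plan, and that document is not shown. The data also survive: daily steps can be re-summarised at any time. This weakens the point without removing it, because the protocol itself fixes a plain interval mean and the run-in baseline, and those two choices produce the contrast.

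The assumption that visits add steps is open to challenge. For the first injection, "The patient will stay in the outpatient ward for at least 6 hours after the first Daratumumab injection", with intravenous access kept in place, and later injections carry a 2-hour observation. Much of that time may be sedentary, and the mode of travel is not described. This stands: the sign cannot be settled from the documents.

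The planned analyses also limit the damage. If the week 10-12 mean includes the week-12 visit, the comparison with week 12 has one visit day on each side. That cancels the visit day but not reduced steps on following days, since no visit precedes that interval.

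Steps is one of several secondary variables in an exploratory study whose primary outcome is safety, and the protocol says that its size rules out firm efficacy conclusions. This stands, and it limits the weight of the point.

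A reader might infer that any rise in steps would be an attendance artefact, or that the bias favours the drug. The documents support neither. The direction is unknown, the first two patients do not follow the schedule, and the later visit-free means offer a check within the study.

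**Conclusion.** The point holds for the early time points. On the standard schedule, one day in 14 is a hospital day in each 2-week step mean from week 12 to 20, against one or two days in the 84-day baseline. The week 16, 18 and 20 comparisons can therefore partly measure attendance.

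The visit counts come from the protocol; the effect size does not. The range of about -8% to +17% takes one baseline visit day, visit-day steps 1.25 to 4 times usual, and up to three following days at half the usual steps. Within that range the effect can also be nil.

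Without maintenance, a change that persists at weeks 24, 28, 40 and 48 would not be explained by scheduled clinic or injection visits, subject to where NIRS sessions fall. The improvement is worth making because it is cheap and protects the only device-measured efficacy outcome; the point does not invalidate that outcome.

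**What to change.** In Fitbit armband data, Endpoints and statistical analyses, and Assessment during follow-up, keep the all-day interval mean and add a second one. In the second, leave out each hospital-visit day and a pre-set number of following days, for example two, from every run-in and follow-up interval. Following days should be dropped even when they fall in the next interval. Count NIRS and unscheduled hospital visits as visit days, and state which interval a boundary day belongs to. Do not drop the visit day alone. Interpret early changes in steps against the visit-free intervals.

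This removes the attendance shift only if after-effects last no longer than the days left out. With two following days dropped, a third day at half steps would leave (10 + 0.5)/11, or -4.5%. That is a reason to show both means.

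The cost is a sentence or two in the text, a few lines of code, and about three fewer days in each affected 14-day mean. Daily steps and visit dates should already be held, and no clinical procedure changes.
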